#### Recruitment

As per WS1, children and their parents will be recruited via general, community and/or specialist paediatric services in English NHS Trusts, and children’s nutrition and dietetic services attached to, or working into, these services. Based on estimated numbers of children using a home-blended diet we plan to recruit from around 20 NHS Trusts. For WS2 we will also plan to recruit from children’s hospices in England and via social media, as recommended by the parent advisors for the study.

Families will be recruited primarily in routine clinic appointments with paediatricians or dietitians, but families may also be invited by post, telephone and via social media. In WS2, families must be supported by a recruiting NHS Trust or children’s hospice to take part, in order for clinical data to be obtained in the study. In WS2, clinicians will introduce the study and obtain consent from parents and children where possible for the study team to contact them. Consent to participate in the study will be sought by the study team, with appropriate consent/assent processes used depending on the age and capacity of participating children. For young adults (16–18 years), an assessment of capacity in line with the Mental Capacity Act will be undertaken by the clinician at the consent to contact stage.

All families will receive a full study information pack about the study, which will contain relevant participant information sheets and study consent forms depending on the child/young person’s capacity. For young adults who lack capacity, we will identify an appropriate personal consultee to provide advice about the young adults’ views and wishes about taking part in the study, using appropriate consultee information sheets and consultee declaration forms.

Consent processes are as follows:

*Young adults age*
*d*
*16*
*–*
*18*
*years*
*with capacity*. Young adults and parents will provide separate consent for their own participation.
*Y*
*oung adults age*
*d*
*16*
*–*
*18*
*years*
*without capacity*. No consent will be taken. Young adults will take part in the study if the consultee advises that they would not have any objections to taking part. Parents will consent separately for their own participation in the study.
*Children and young people age*
*d*
*7*
*–*
*15*
*years*
*who can understand information about the study and express an opinion about taking part*. Parents will provide consent and the child/young person will provide written or verbal assent. A simplified version of the assent form will be used for children aged 7–11 years, with a standard version used for young people aged 12–15 years. Parents will provide separate consent for their own participation.
*All other children and young people under the age of*
*16*
*years*. Parents will consent for their child and themselves.

#### Data collection

Data will be collected at three time points: at baseline and then at 9 and 18 months. At each time point, data on a range of outcomes as well as relevant clinical and feeding information will be collected from parents/children/young people and clinicians. See table 2 for summary of proposed outcomes and data sources (these are subject to change following WS1).

**Table 2 T2:** Proposed variables and data sources for WS2

Variable	Type of variable	Proposed measure	Source	Timings of data collection (months)		
				0	9	18
Participant characteristics/predictors						
Age	Predictor	Date of birth	Parent	√		
Ethnicity		Census groups	Parent	√		
Deprivation		Index of Multiple Deprivation (based on postcode)	Parent	√	√	√
Parental educational attainment		Census groups	Parent	√		
Household composition		Number of children, marital/living status	Parent	√	√	√
Diagnosis			Paediatrician	√		
Comorbidities			Paediatrician	√	√	√
All medications			Paediatrician	√	√	√
Complexity		Disability Complexity Scale^23 24^	Paediatrician	√	√	√
Length of time gastrostomy fed at T0		Months/years	Parent	√		
Comparator						
Diet: formula/blended	Main grouping variable		Parent	√	√	√
Outcomes						
Nutritional content of feeds	Outcome	Commercial for formula	Dietitian/parent	√	√	√
		myfood24^15^	Parent	√	√	√
Anthropometric data	Outcome	Height or length Weight Triceps skinfold thickness or mid-arm circumference	Dietician Paediatrician	√	√	√
Gastrointestinal symptoms	Outcome	PedsQL gastrointestinal^19^	Parent/child	√	√	√
Child quality of life	Outcome	PedsQL generic module^18^	Parent/child	√	√	√
Parental quality of life	Outcome	EQ-5D-5L^25^ Parenting Morale Index^26^	Parent	√	√	√
Healthcare use	Outcome	Client service receipt inventory^27^	Parent	√	√	√
	Outcome	Number of hospital admissions Number of accident and emergency (A&E) attendances	HES data	√	√	√
Safety	Outcome	Tube blockages Number of stoma infections Number of gastrointestinal infections	Parent			
	Outcome	Number of hospital admissions and A&E attendance associated with child’s gastrostomy/diet	HES and parent	√	√	√
Family resource use	Outcome	Time preparing feeds; impact on other caring/parenting Financial costs	Parent	√	√	√
Non-staff NHS resource use	Outcome	Cost of formula and packaging Dietetic resources	Dietitian	√	√	√

EQ-5D-5L, 5-level version of EuroQol-5 Dimension; HES, Hospital Episodes Statistics; NHS, National Health Service; PedsQL, Pediatric Quality of Life Inventory; WS2, workstream 2.

The majority of the data will be collected via parent questionnaire administered according to parent preference (postal vs online; parents will also be offered telephone interview). Parents whose children receive home-blended food will also be required to provide dietary information via the online myfood24 tool,^15^ or via a paper food diary or telephone call with the research team if using the online tool is not possible. Where appropriate, participating children and young people will also be asked to complete a short questionnaire (eg, to self-report QoL). Up to three reminders via text and/or post will be used at each time point. A small incentive voucher of £20 will be provided to each family after return of the questionnaires at each time point.

Clinical information (eg, diagnoses, medications, anthropometry) will be collected from children’s paediatrician and/or dietitian. Dietitians will also provide details about formula feeds used by participating children. Finally, we will use routine healthcare data through linkage undertaken by NHS Digital to the HES data (inpatient, accident and emergency (A&E), outpatient) and the Office for National Statistics (ONS) death certificate data.

#### Data analyses

The data quality of each data item collected will be assessed when the data are collected or received by the research team. Appropriate attempts will be made to obtain missing or out-of-value data. A review of the collected data will be undertaken after the first 25 participants have completed baseline questionnaires to check for any systematic issues with the data collection.

A statistical analysis plan will be developed and signed off prior to analysis. Analysis will follow Strengthening the Reporting of Observational Studies in Epidemiology^16^ and Reporting of Studies Conducted Using Observational Routinely-collected Data^17^ guidelines. Descriptive statistics of clinical and demographic characteristics of the study population at baseline will be used to examine differences between the groups of children who are predominantly formula fed and those who use home-blended diets.

Children will be grouped into those who are on a predominantly blended diet or formula diet at baseline by:

Home-blended group if most of their nutritional intake is provided via home-blended diet. This categorisation will be informed by WS1 and in consultation with the SSC.Formula fed if most of their diet comes from formula.

Most of the proposed outcome measures will require scoring or aggregation before the statistical modelling can be undertaken:

The PedsQL generic scale^18^ and PedsQL gastrointestinal symptoms module^19^ will be scored as per the guidelines and transformed to a score of 0–100.The height (or length) and weight will be used to calculate an age and sex-adjusted body mass index (BMI SD score (SDS)).The myfood24 data programme analyses the nutritional content of the home-blended diet and will compute the calorie intake and the macro/micronutrient content of the feed and any oral feeds. The same data for the formula fed group will have been obtained, via the dietitian, from the commercial supplier.The parent-reported number of site infections and other tube-related complications will be reported as total counts for each child.The diagnostic (International Classification of Diseases, Tenth Revision)^20^ and procedural codes (OPCS Classification of Interventions and Procedures) in the HES data will be used to identify admissions which were related to complications of the gastrostomy tubes or infections. The number of admissions and A&E attendances will be calculated for each child. Length of stay for each admission will also be calculated for the resource use analyses.Parent QoL. The EuroQol-5 Dimension (EQ-5D) visual analogue scale is scored 0–100 and the five-component scale of the 5-level version of EuroQol-5 Dimension (EQ-5D-5L) will be converted to a single score using a UK-specific value set.^21^ The 10-item Parenting Morale Index is scored from 0 to 100.

For all outcomes we will report the baseline score, follow-up scores and change score.

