Recent national surveys of paediatric dietitians in the UK^4^ and the USA^5^ both found that more than half of respondents would recommend the use of a home-blended diet (56% and 58%, respectively). In the UK, however, that recommendation was to use home-blended food as a supplement to formula feeds rather than their exclusive use.

At the same time, concerns have been raised by professional organisations, including the European Society for Paediatric Gastroenterology Hepatology and Nutrition and British Dietetic Association, about the risks associated with a diet of home-blended foods. These include: nutritional inadequacy, microbial contamination and blockage of the gastrostomy tube. Policy/position statements from such organisations do not recommend that children (or adults) are fed home-blended foods through their gastrostomy tubes.^9^ Importantly, it was acknowledged in these guidelines that the evidence for this statement is low and further research is likely to have an impact on this recommendation.

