#### Assessing safety (objective 2) and benefits (objective 3)

The safety and benefits of blended diet compared with formula diet will be assessed using multivariable regression analyses. The type of regression will depend on the outcome of interest: logistic (tube blockage, appropriate nutritional content; yes/no), linear (PedsQL gastrointestinal module score, BMI SDS or upper arm circumference, calories, Parenting Moral Index (PMI), EQ-5D), Poisson or negative binomial (number of A&E or hospital admissions for infections or complications of gastrostomy tube). Each analysis will account for the multiple confounding factors in this population (age, underlying diagnoses, comorbidities, outpatient attendance, parental factors, socioeconomic status) and the main covariate of interest will be feeding status (blended vs formula). Study site will be added as a random effect to the models to allow for site-level variation. Estimates and 95% CIs will be reported from the regression model for each outcome measure.

The flow of participants through the study will be detailed including the number of individuals contributing to each analysis. The amount of missing data will be summarised for each outcome measure and multiple imputation will be used to assess the robustness of the results. Results will be compared with the complete case analyses and important differences discussed. Sensitivity analyses will be considered to explore departures from the missing at random assumption.

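### The only growth score stated from height and weight is BMI SDS, compared as a mean between diets, so a proportionate growth deficit or a widening of both tails could be missed

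*Protocol article*

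**What the plan says.** The Introduction lists the risks that professional bodies have raised about blended diets: "nutritional inadequacy, microbial contamination and blockage of the gastrostomy tube". Objective 2 is to compare the safety of the two diets.

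Table 2 (Data collection) has these anthropometric items at months 0, 9 and 18: "Height or length Weight Triceps skinfold thickness or mid-arm circumference". The Data analyses section says what becomes of the first two: "The height (or length) and weight will be used to calculate an age and sex-adjusted body mass index (BMI SD score (SDS". It states no other score derived from height or weight. It also promises baseline, follow-up and change scores for every outcome.

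The section on assessing safety and benefits assigns the models. The linear list reads "linear (PedsQL gastrointestinal module score, BMI SDS or upper arm circumference, calories, Parenting Moral Index (PMI), EQ-5D". The binary list reads "logistic (tube blockage, appropriate nutritional content; yes/no" and has no growth category. Triceps skinfold, one of the two arm options in Table 2, is not in any model list.

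**The concern.** If a blended diet supplied too little over time, slower growth in length and weight would be one visible result. The stated scoring reduces two measurements to one ratio, and the stated model reduces that ratio to a difference in means. Each step can lose the signal:

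- The ratio does not respond when weight falls with the square of height.
- The mean does not respond when some children become thinner and others heavier by similar amounts.

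The arm measure is a weak back-up. Its link to BMI SDS is an undefined *or*, it is also analysed as a mean, and it says nothing about length. Clinicians may record skinfold instead, for which no analysis is stated.

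At stake is how a null result is read. Similar mean BMI SDS in the two groups could be taken as reassurance about growth that the analysis cannot give.

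**Working it through.** **1. The plan's own precision figure.** The Sample size section gives 300 children, twice as many formula fed as blended, hence 200 and 100. It states a within-group margin of at most 10% for a proportion. With 1.96·√(p(1−p)/n) at p = 0.5, the margin is 9.8% for n = 100 and 6.9% for n = 200, so the figure reproduces. No precision is stated for BMI SDS or any growth measure.

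**2. What BMI does when height and weight fall together.** BMI = weight/height². If height is a fraction d below expected, BMI is unchanged when weight is 1 − (1 − d)² below expected.

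| Height below expected | Weight deficit leaving BMI unchanged |
|---|---|
| 5% | 9.75% |
| 10% | 19% |
| 15% | 27.75% |

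A child 5% short and 10% light has BMI 0.90/0.95² = 0.997 of expected. The cancellation is not general: at 5% short and 15% light, BMI is 0.85/0.95² = 0.94 of expected. So BMI SDS can stay near normal in a growth-restricted child, but need not.

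**3. What the mean does when both tails grow.** None of these inputs is in the documents; they show the mechanism only. Assume BMI SDS is N(0,1) in the formula group. In the blended group, assume half the children are shifted down and half up by s. The mean difference is ½(−s) + ½(s) = 0 for every s. The share below −2 is ½[Φ(−2 + s) + Φ(−2 − s)], and by symmetry the share above +2 is the same.

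| s (SDS) | Mean difference | Share below −2 (2.3% in formula group) | Power, 200 v 100, to detect the change in share |
|---|---|---|---|
| 0.5 | 0 | 3.7% | 12% |
| 0.75 | 0 | 5.4% | 32% |
| 1.0 | 0 | 8.0% | 62% |
| 1.5 | 0 | 15.4% | 97% |

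The last column limits the remedy. A share of 8.0% among 100 blended children has a 95% half-width of 1.96·√(0.08·0.92/100) = 5.3 percentage points.

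**4. Precision of the added scores.** For any SDS outcome at 200 v 100, the unadjusted 95% half-width of a mean difference is 1.96·SD·√(1/100 + 1/200). This is 0.24, 0.36 or 0.48 for an assumed SD of 1, 1.5 or 2. At the same SD, a height-for-age or weight-for-age score is as precise as the BMI SDS comparison already planned.

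**5. Table 2 against the model list.** Table 2 allows "Triceps skinfold thickness or mid-arm circumference". The model list has "BMI SDS or upper arm circumference". A child measured by skinfold can contribute to BMI SDS but has no stated analysis of the arm measure.

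**The case against.** The strongest reply has four parts.

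- **The named risk is tested directly.** Nutritional content is modelled as appropriate or not, calories are modelled, and macro- and micronutrients are computed for both diets. This stands as far as it goes. It means BMI SDS is not the only evidence on nutrition. But these outcomes describe what goes in, not whether the child grew.
- **Height and weight are not discarded.** Table 2 lists them as outcome measures, and all outcomes get baseline, follow-up and change scores. The model list also leaves out other planned outcomes, such as the PedsQL generic score, so it may not be exhaustive. A reader might infer that height and weight are never analysed in their own right, and the documents do not support that. What is absent is any stated age- and sex-standardised comparison of height or weight between diets, and raw values across 6 months to 18 years cannot replace it.
- **Detail belongs in the analysis plan, and outcomes may change after WS1.** That would answer a complaint about omission. Here the article positively states the derived score and its model, and an analysis plan that follows it inherits the limitation.
- **The tail example is hypothetical, and tail shares will be imprecise.** Both are true. The shares therefore belong in a descriptive supplement, not among the main comparisons.

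**Conclusion.** The point holds in a limited form. The stated growth analysis, a linear comparison of BMI SDS with arm circumference as an undefined alternative, can miss a proportionate deficit in height and weight and a spread into both tails. The first part rests on algebra (0.997 of expected BMI at 5% short and 10% light). The second rests on assumed shifts of 0.5 to 1.5 SDS, which take the share below −2 from 2.3% to between 3.7% and 15.4% with no change in the mean.

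Three stronger readings go too far:

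- A reader might infer that BMI SDS always stays normal in a stunted child. It does so only when weight falls roughly with height squared.
- A reader might infer that objective 2 will be answered wrongly. That objective also draws on nutritional content, tube blockage, infections and admissions, so the risk is a gap in the growth evidence.
- A reader might infer that the protocol treats a higher BMI SDS as better. No section says so.

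The study can run as designed, but the change should be made before the analysis plan is signed off.

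**What to change.** 1. In Data analyses, add height(length)-for-age SDS and weight-for-age SDS to the scoring list. In the safety and benefits section, put both into the same adjusted linear models as BMI SDS, with change from month 0.
2. Report by diet, with 95% CIs, the proportions below −2 and above +2 BMI SDS. Label these as descriptive and say that they are imprecise with about 100 blended children.
3. Replace the *or* between BMI SDS and upper arm circumference with *and*. State an analysis for triceps skinfold where that was the measure recorded, so that Table 2 and the model list agree. Requiring one common arm measure is not needed: anthropometry comes from each child's own paediatrician or dietitian, so it would change data collection and not only analysis wording.

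**Cost.** The first two items use height and weight already collected at 0, 9 and 18 months, and the third is wording. A few more outcomes have to be reported. Height is harder to measure in children with contractures, but BMI SDS already depends on the same height.

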#### Eligibility criteria

Children (aged 6 months to 18 years inclusive) who receive most or all of their nutrition via gastrostomy tube. Parents of participating children will also take part in the study. We are including child and parent dyads in order to measure child and parent outcomes (eg, QoL); therefore, children who do not live with a biological or adoptive parent are not eligible to take part. The study is limited to families who reside in England (see table 1 for summary of inclusion and exclusion criteria).

**Table 1 T1:** Eligibility criteria

	Eligible	Ineligible
A	Child is at least 6 months old and under 19 years.	Infants up to 6 months and young people who are 19 years and older.
B	Child is gastrostomy feed dependent.	Child has another type of feeding tube (eg, nasogastric, jejunostomy).
C	Child receives most or all of their nutrition via the gastrostomy.	
D	Child is living with parent(s): biological or adoptive.	Child is not living with a parent (eg, in residential setting or foster care).
E	Family resident in England.	Family not resident in England.

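### Nutritional intake is captured by different methods in the two diet groups, so the calorie and nutritional-content comparisons are not like with like; size and direction are unknown

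*Protocol article*

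**What the plan says.** All places are in the protocol article, Workstream 2.

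- **Blended food, collection.** Data collection: "Parents whose children receive home-blended food will also be required to provide dietary information via the online myfood24 tool", with a paper food diary or a telephone call as alternatives.
- **Blended food, scoring.** Data analyses: myfood24 will "compute the calorie intake and the macro/micronutrient content of the feed and any oral feeds".
- **Formula, collection.** Data collection: "Dietitians will also provide details about formula feeds used by participating children". No dietary record is asked of parents whose child receives formula only.
- **Formula, scoring.** Data analyses: "The same data for the formula fed group will have been obtained, via the dietitian, from the commercial supplier".
- **Table 2.** Under nutritional content of feeds, the measure for formula is commercial data, with dietitian and parent jointly named as source. The measure for blended food is myfood24, with the parent as source.
- **Who may eat by mouth.** Eligibility criteria, Table 1: "Child receives most or all of their nutrition via the gastrostomy". Data analyses, group definition: "Formula fed if most of their diet comes from formula". Neither excludes oral food.
- **What is compared.** The section on assessing safety and benefits plans a linear model for calories and a logistic one for nutritional content: "logistic (tube blockage, appropriate nutritional content; yes/no". Feeding status is the main covariate in each.

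**The concern.** The protocol treats the two data streams as the same data. One is recorded intake by tube and mouth; the other is, on its face, the nominal content of a product. Feeding group decides which method is used, and feeding group is also the exposure. The measurement difference is therefore aligned with the contrast being estimated. Adjusting for confounders, adding a random effect for site or imputing missing values cannot remove it, because none of these carries information on the unrecorded intake.

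The stakes are real. In the Introduction, nutritional inadequacy is the first risk listed among professional bodies' concerns about blended diets, and assessing safety is objective 2. Calories and nutritional content are the outcomes that address that risk most directly. Intake that was never collected cannot be recovered by a later analysis plan.

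**Working it through.** **1. The two streams side by side**

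| | Receives home-blended food | Formula only |
|---|---|---|
| Who records | Parent | Dietitian, from supplier (Table 2 also names the parent) |
| Tube feed | As recorded | Product composition; amount given not addressed |
| Oral food | Included | No stated route |
| Enters the models as | Calories; appropriate content | Calories; appropriate content |

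A child classed as formula fed who also gets some blended food falls under the myfood24 requirement, so methods may also differ within the formula group.

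**2. The plan's own precision, as a yardstick**

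The protocol gives no figure for intake. Its Sample size section assumes 300 children at 2:1, so 200 formula and 100 blended, and a margin of error of at most 10% for a proportion within each group. With p = 0.5, 1.96 × √(0.25/100) = 9.8% and 1.96 × √(0.25/200) = 6.9%, so that figure reproduces.

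**3. Effect of omitting oral food**

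Assume equal true intake in both groups and complete recording in the blended group. Let q be the share of formula children who eat by mouth and f the oral fraction of their energy. Mean formula intake is understated by q × f. Both values are assumptions; the documents give neither.

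| q | f | q × f |
|---|---|---|
| 25% | 10% | 2.5% |
| 50% | 10% | 5% |
| 50% | 20% | 10% |
| 100% | 20% | 20% |

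**4. What such a gap does to the linear model**

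Express intake as a percentage of requirement, with an assumed mean of 100 and SD of 20. The SE of the difference is 20 × √(1/100 + 1/200) = 2.45, and the 95% half-width is 1.96 × 2.45 = 4.80. For a pure measurement gap b and no true difference, the probability of a significant two-sided 5% result is 1 − Φ(1.96 − b/2.45) + Φ(−1.96 − b/2.45):

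- b = 2.5 points: 0.175
- b = 5 points: 0.53
- b = 10 points: 0.98

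**5. What it does to a yes/no outcome based on amount**

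Assume intake has mean 105 and SD 20, with a cut-off of 100. True adequacy is 1 − Φ(−0.25) = 59.9% in both groups. Among formula children who eat by mouth, measured intake has mean 105(1 − f) and SD 20(1 − f).

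- q = 50%, f = 10%: 0.5 × 59.9% + 0.5 × 38.0% = 48.9%, a false gap of about 11 points.
- q = 50%, f = 20%: 0.5 × 59.9% + 0.5 × 15.9% = 37.9%, a false gap of about 22 points.

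**6. Why the sign is open**

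Suppose the formula amount is taken from the prescription and only a fraction d of it is delivered, every formula child has oral fraction f, and blended diaries under-record by u. With true intake 100 in both groups, measured blended minus formula is 100(1 − u) − 100(1 − f)/d:

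- f = 10%, d = 1, u = 0: +10
- f = 10%, d = 0.9, u = 0: 0 (the errors cancel)
- f = 10%, d = 1, u = 10%: 0
- f = 0, d = 0.9, u = 0: −11.1

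**The case against.** The best reply is that the article condenses a fuller protocol and leaves the method open. Table 2 names the parent as a joint source for formula data and is declared subject to change after Workstream 1. Workstream 1 asks about oral feeding and about collecting nutritional data, the steering committee then chooses the tools, and data collection is reviewed after 25 participants. The phrase about the same data directly follows a mention of oral feeds, so omission of oral food is an inference and not a statement.

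Much of this stands. It would be too strong to say that no formula child has any food record, or that the plan excludes oral intake. The reply does not remove the point: the measure for formula in Table 2 is still commercial data, the named origin is still the supplier, and dietary records are required only where blended food is given.

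A reader might also infer that, because the Introduction calls formula complete nutrition, almost every formula child will count as adequate, leaving an odds ratio that cannot be estimated. The documents do not support this. Completeness there describes a product and does not show that each child's volume meets requirements. The article does not define appropriate nutritional content, and if it is judged on amount, omitted oral food would lower adequacy in the formula group.

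It is also fair that no primary outcome is named, and that anthropometry offers a nutritional endpoint whose listed measures and sources do not differ by diet.

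**Conclusion.** The point holds as a lack of comparability. Followed as written, the plan compares recorded intake by tube and mouth with supplier-derived feed content, by the same factor that decides the method. This affects calories and appropriate nutritional content only; PedsQL, anthropometry and hospital-record (HES) outcomes are untouched.

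The conclusion rests on two readings: that a supplier can give composition only, and that no unstated route captures oral food in children fed formula only. The 2.5% to 20% range, the SD of 20% of requirement and the adequacy cut-off are illustrations, not estimates. A reader might infer that formula intake must come out too low; the documents do not support this, because undelivered feed and under-recorded diaries act in the opposite direction and can cancel or reverse the gap.

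**What to change.** Collect total intake (tube feed actually given plus all oral food) in both groups, with the same record over the same days. Use supplier or dietitian data only for the nutrient composition of the formula. The tools are already in the study (myfood24, paper diary, telephone), and Table 2 is open to revision after Workstream 1. The cost is a small extra response burden for formula families.

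If that burden is refused, compare tube-feed content only in both groups, provided tube and oral entries can be separated in the blended record, which the article does not say. Label the result as recorded versus prescribed or nominal feed content, and do not interpret it as a comparison of total intake or adequacy. This fallback removes only the oral-food part of the mismatch; the gap between nominal and delivered feed remains, and separating the entries takes some work.
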